**Methods/Design:**

The study is a one-month randomized controlled trial with a two parallel group design and a 12-month naturalistic follow-up. A sample of 130 consecutive adult inpatients with unipolar depression and Montgomery-Asberg Depression Rating Scale score over 18 will be recruited. The study is carried out in the university hospital section for mood disorders in Lausanne, Switzerland. Patients are assessed upon admission, and at 1-, 3- and 12- month follow-ups. Inpatient therapy is a manualized brief intervention, combining the virtues of inpatient setting and of time-limited dynamic therapies (focal orientation, fixed duration, resource-oriented interventions). Treatment-as-usual represents the best level of practice for a minimal treatment condition usually proposed to inpatients. Final analyses will follow an intention–to-treat strategy. Depressive symptomatology is the primary outcome and secondary outcome includes measures of psychiatric symptomatology, psychosocial role functioning, and psychodynamic-emotional functioning. The mediating role of the therapeutic alliance is also examined. Allocation to treatment groups uses a stratified block randomization method with permuted block. To guarantee allocation concealment, randomization is done by an independent researcher.

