### Power calculation

Based on previous studies, at least moderate effect sizes of psychodynamic psychotherapy on patient outcome (e.g. f = .25 for severity of depressive symptomatology) could be expected. Power analysis (with two-tailed alpha set at .05 and a power of .80) for repeated measure ANOVA indicates that 108 patients (54 in each group) are sufficient to detect the expected effects [34]. With 22% of non-completers, an *intent-to-treat sample* of 138 patients (69 in each group) is required in order to have a *completer sample* of 108 patients. All analysis will be done on the two samples.

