#### Therapists’ selection and training

All psychotherapists (N between 10 and 15) are resident psychiatrists in an advanced or completed stage of a 4-year psychotherapy training program in psychodynamic psychotherapy and having attended training in brief psychodynamic psychotherapy and IBPP. The IBPP training course lasts two years (two hours weekly). The first year includes theoretical presentation, role playing and case presentation. The second year is devoted to group supervision. Training is delivered by three expert trainers of the Lausanne University Medical School, who are agreed supervisors for the psychodynamic psychotherapy and authors of the IBPP manual.

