### Data analysis

Final analyses will follow an intention-to-treat strategy comparing patients in the groups to which they were originally randomized. Clinical Significance method will be used to estimate rates of response (reliable improvement), remission (clinical significance), recovery (maintained clinical significance) and relapse (deterioration) [63]. For short-term outcome, repeated-measure analyses of variance (ANOVA) and analyses of covariance (ANCOVA - controlling for pretreatment scores and patient’s age) will be used on all outcome measures. For long-term outcome, linear mixed-effects models will be preferred, as well as for therapist and alliance effects on outcome [64]. Last Observation Carried Forward (LOCF) will be used for missing data when appropriate. Latent class analysis (using Latent Gold 4.5) will be done to explore the effect of moderating variables.

Cost-effectiveness analysis will be done in collaboration with the Institute of Health Economics and Management (IHEM) of the University of Lausanne. An economist at the IHEM will be in charge of the data analysis. The economic evaluation will be conducted from the perspective of the health system. Primary outcome will be remission in depressive symptomatology at 12 months. The comprehensively measured service costs between the two treatments will be compared with the difference in change in the primary outcome measure and with the difference between the treatments in QALYs gained.

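### The one-month treatment comparison (ANOVA/ANCOVA) has no therapist term although only IBPP patients are nested in psychotherapists; if the therapist ICC is above zero, its standard error is understated

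*Protocol article*

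**What the plan says.** In the protocol article, Data analysis assigns two methods to short-term outcome: repeated-measures ANOVA, and ANCOVA adjusted for the pretreatment score and the patient's age. No therapist term is named. The next sentence reads: "For long-term outcome, linear mixed-effects models will be preferred, as well as for therapist and alliance effects on outcome".

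Therapists' selection and training gives the number of IBPP providers: "All psychotherapists (N between 10 and 15) are resident psychiatrists". The section on IBPP describes 12 sessions of 45 minutes over four weeks.

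TAU has its own providers. Its section lists sessions with a psychiatric resident twice a week, and Supervision says that the TAU psychiatrists are supervised individually. Strengths and limitations states that IBPP is given on top of TAU. The resident layer is therefore present in both arms, and only the psychotherapist layer is confined to IBPP.

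Power calculation uses "f = .25 for severity of depressive symptomatology", "with two-tailed alpha set at .05 and a power of .80", and concludes that "108 patients (54 in each group) are sufficient to detect the expected effects". It mentions neither an ICC nor a design effect.

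**The concern.** Patients who share a psychotherapist may have correlated outcomes, and here that can happen through the psychotherapist in one arm only. An ANOVA or ANCOVA without a therapist term counts each IBPP patient as an independent unit. Any variation between psychotherapists then enters the treatment contrast without entering its SE. A separate mixed model that describes therapist effects does not repair the SE of the ANOVA/ANCOVA contrast.

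The short-term contrast is where this matters most. The design is a one-month randomized trial followed by naturalistic follow-up, and the sample size is built on repeated-measures ANOVA. At stake are a confidence interval that is somewhat too narrow, a type I error above the nominal 5%, and a power statement that holds only without therapist clustering.

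**Working it through.** **The plan's own figures.** The power section gives f = 0.25, two-sided alpha 0.05 and power 0.80, but not the number of measurements or their correlation, so 108 cannot be derived uniquely. For the between-group F test with m measurements and correlation ρ, the noncentrality is λ = f²·N·m / (1 + (m − 1)ρ), with 1 and N − 2 degrees of freedom. One measurement needs N = 128. Two measurements need 106 at ρ = 0.65 and 110 at ρ = 0.70; three at ρ = 0.75 need 108. So 108 is attainable with plausible unstated values and is not shown to be wrong. None of these calculations contains a clustering allowance.

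The next step uses "With 22% of non-completers": 108 / 0.78 = 138.5, against the stated "138 patients (69 in each group) is required". The difference is rounding.

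**Inputs for the nesting check.**
- IBPP completers: 54 (Power calculation). The nominal 0.80 belongs to this sample.
- Psychotherapists: k = 10 to 15 (Therapists' selection and training).
- Therapist ICC: not given. Assumed 0 to 0.10; it refers to the outcome after covariate adjustment.
- Equal total variance in the arms, equal caseloads and normal approximations: assumed.

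**Formulas.**
- Patients per therapist: c = 54 / k, which is 54/15 = 3.6 to 54/10 = 5.4.
- Design effect in the IBPP arm: DE = 1 + (c − 1)·ICC. In the TAU arm it is 1.
- True SE / naive SE: R = √((DE + 1)/2).
- Actual two-sided type I error of the naive test: 2·(1 − Φ(1.96/R)).
- Power when analysed correctly: Φ(2.80/R − 1.96).
- Completers needed: 108·(DE + 1)/2.

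**Example** (k = 10, ICC 0.10): DE = 1 + 4.4 × 0.10 = 1.440; R = √(2.440/2) = 1.105; type I error = 2·(1 − Φ(1.774)) = 0.076; power = Φ(2.535 − 1.96) = 0.718; completers = 108 × 1.22 = 131.8.

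| ICC | therapists | c | DE | R | type I error | power | completers |
|---|---|---|---|---|---|---|---|
| 0 | any | – | 1.000 | 1.000 | 0.050 | 0.80 | 108 |
| 0.01 | 15 | 3.6 | 1.026 | 1.006 | 0.0515 | 0.795 | 109.4 |
| 0.01 | 10 | 5.4 | 1.044 | 1.011 | 0.0525 | 0.791 | 110.4 |
| 0.05 | 15 | 3.6 | 1.130 | 1.032 | 0.0575 | 0.775 | 115.0 |
| 0.05 | 10 | 5.4 | 1.220 | 1.054 | 0.0628 | 0.758 | 119.9 |
| 0.10 | 15 | 3.6 | 1.260 | 1.063 | 0.0652 | 0.750 | 122.0 |
| 0.10 | 10 | 5.4 | 1.440 | 1.105 | 0.0760 | 0.718 | 131.8 |

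R is how much larger the true SE is. The naive SE falls short by 1 − 1/R, which is 0.6% at R = 1.006 and 9.5% at R = 1.105.

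**Sensitivity.**
- Intention-to-treat sample, 69 in the IBPP arm (4.6 to 6.9 per therapist), ICC 0.01 to 0.10: R is 1.009 to 1.138 and type I error 0.052 to 0.085. The naive SE is then at most 1 − 1/1.138 = 12% too small.
- Unequal caseloads (coefficient of variation 0.5), 54 completers, 10 therapists, ICC 0.10: DE = 1 + (1.25 × 5.4 − 1) × 0.10 = 1.575, R = 1.135, type I error 0.084, power 0.695.
- With only 10 to 15 therapists, small-sample degrees of freedom would widen a correct interval a little further.

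**The case against.** The strongest reply is that the article already deals with therapists. The clause on therapist and alliance effects assigns them to mixed models and can be read as covering outcome at any time. How the term is coded, and with which degrees of freedom, is detail that an article may leave to the full protocol or analysis plan. This stands in part: a reader might infer that the plan ignores therapist effects altogether, and it does not. But the article does name the method and covariates for the short-term contrast, and that method has no therapist term. This is a stated choice, not an omitted detail.

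A second reply is that TAU is not free of providers. This also stands. A reader might infer that TAU patients have no individual clinicians; in fact residents see patients in both arms. Because that layer is common to the arms, it does not remove the one-sided nesting in psychotherapists. The proposed model does not, however, address correlation among patients who share a resident.

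A third reply is that the harm depends on an ICC nobody has stated, and that 10 to 15 therapists with about four to five completers each will estimate it poorly. Both are true. They limit how strongly the point can be put and make a prespecified sensitivity analysis a defensible minimum. They do not make independence the better assumption for the primary randomized comparison.

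Finally, recruitment is closed, so the sample size cannot respond to this. The analysis still can, because the article says follow-up is continuing.

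**Conclusion.** The point holds conditionally, with a small to moderate effect. If the therapist ICC is above zero, the planned one-month ANOVA/ANCOVA understates the SE of the treatment contrast. For an assumed ICC of 0.01 to 0.10 and 54 completers per arm, the true SE is about 1% to 10% larger, type I error is 0.0515 to 0.076, and power is about 0.795 to 0.72 instead of 0.80. At ICC 0.05 the figures are 3% to 5%, 0.058 to 0.063, and 0.775 to 0.758. At ICC 0 there is no effect.

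Two stronger readings are tempting and are not supported. One is that the SE is certainly too small: the article gives no ICC, so this cannot be stated as fact. The other is that power falls to about 0.69: that figure applies the nominal 0.80, which belongs to 54 per arm, to caseloads from 69 per arm, and takes the highest assumed ICC with the fewest therapists.

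The point merits a change because a better method is available at little cost and the plan already uses that model class elsewhere.

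**What to change.** For the one-month contrast, specify a partially nested mixed model: a random psychotherapist effect for IBPP patients only, each TAU patient as a separate unit at that level, arm-specific residual variance, and Satterthwaite or Kenward-Roger degrees of freedom. Keep the pretreatment score and age as covariates. Put the same term into the mixed models already planned for 3 and 12 months. Report the estimated ICC with its interval, and state that the 0.80 power assumes no therapist clustering, with the range above. If ANOVA/ANCOVA must remain the main analysis, the nested model should at least be a prespecified sensitivity analysis.

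The cost is a change of wording in the analysis section and the recording of each IBPP patient's therapist, which should be available because all individual sessions are audiotaped and the therapists are supervised individually. The statistical price is a slightly wider confidence interval and an ICC estimated imprecisely from 10 to 15 therapists.

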#### Psychopathology

##### Depression

Depressive symptoms are the primary outcome. This is assessed by two instruments: (1) The Montgomery-Asberg Depression Scale (MADRS; [39]), a clinician rating measure in 10 items, which serves as our primary outcome measure, and (2) the self-rated version of the Inventory of Depressive Symptom (QIDS-SR_16_; [40]), a 16-item self-report measure of depressive symptoms. To allow for Kaplan-Meyer estimates of speed of response, MADRS is done on a weekly basis. The Depressive Experience Questionnaire (DEQ; Blatt SJ, D’Afflitti J, Quinlan DM: Depressive Experiences Questionnaire, Unpublished research manual, Yale University; 1979) assesses a wide range of life experiences often reported by depressed individuals but not considered symptoms of depression. Its well-established factor structure measures two primary dimensions: interpersonal relatedness and self definition.

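### LOCF is the only missing-data method named and its scope is undefined; it can bias the one-month MADRS contrast if scores are still falling when patients are lost

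*Protocol article*

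**What the plan says.** All of this is in the protocol article; a statistical analysis plan may exist but is not shown.

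- **Missing data** (Data analysis): "Last Observation Carried Forward (LOCF) will be used for missing data when appropriate". No endpoint, visit or condition is attached to the qualifier, and no other method is named.
- **Population** (Data analysis): "Final analyses will follow an intention-to-treat strategy comparing patients in the groups to which they were originally randomized". The Power calculation section adds a completer sample: "All analysis will be done on the two samples".
- **Short-term models** (Data analysis): repeated-measures ANOVA, and "ANCOVA - controlling for pretreatment scores and patient’s age) will be used on all outcome measures".
- **Long-term models** (Data analysis): "For long-term outcome, linear mixed-effects models will be preferred".
- **Primary outcome measure** (Depression): MADRS, and "MADRS is done on a weekly basis".
- **Categorical outcomes** (Data analysis): response and remission rates, then "recovery (maintained clinical significance) and relapse (deterioration". For the economic evaluation: "Primary outcome will be remission in depressive symptomatology at 12 months".
- **Attrition**: Power calculation plans for 22% non-completers, not split by arm. Patients recruitment defines a dropout as a case with fewer than five sessions.

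**The concern.** Repeated-measures ANOVA and ANCOVA need a one-month score for every patient analysed, and LOCF is the only stated way to supply one that is missing. The weekly ratings provide in-treatment scores to carry forward. Patients enter with MADRS above 18, and the inpatient trial cited in the Background reports response in 70% versus 51%, so falling scores over the month are the expected setting. An early score carried forward is then too high, by whatever improvement was still to come.

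If that excess differs between arms, the primary contrast moves with no treatment effect behind it. If the arms improve at different rates, even equal loss shrinks a true difference. LOCF also treats filled values as observed, so the standard errors ignore the uncertainty about them.

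The undefined scope raises a second, conditional question. If LOCF were used for 12-month status, a patient in remission who is then lost would be counted as recovered and not as relapsed. That would reach the recovery and relapse rates and the economic primary outcome.

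**Working it through.** **The plan's own figure.** 108 completers / (1 − 0.22) = 138.5, which agrees with the stated 138. The 22% is therefore an allowance for non-completion. It is not a stated rate of missing MADRS, and no such rate is given.

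**Bias at one month.** Let p be the share of an arm with no one-month score and g the mean fall still to come after the last observed score. For the difference IBPP minus TAU (negative favours IBPP):

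bias = p(IBPP) × g(IBPP) − p(TAU) × g(TAU)

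All trajectories and missing rates below are assumed. The unequal rates average 22%, used only as a proxy.

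*Setting A: no true effect.* Linear 14-point fall over four weeks (3.5 per week), loss completely at random, last visit uniform over weeks 0 to 3, 65 per arm.

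- g = (14 + 10.5 + 7 + 3.5) / 4 = 8.75 points in both arms.
- 27% vs 17% missing: 0.10 × 8.75 = 0.9 points.
- 30% vs 14% missing: 0.16 × 8.75 = 1.4 points.
- Simulation (4,000 trials, week-to-week correlation 0.7, SD rising to 9):

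| Missing IBPP / TAU | Bias | Type I error |
|---|---|---|
| 27% / 17% | +0.89 | 0.083 |
| 30% / 14% | +1.41 | 0.140 |
| 14% / 30% | −1.37 | 0.140 |
| 22% / 22% | −0.01 | 0.049 |

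- ANCOVA on observed scores under the same completely-at-random loss: bias about 0, type I error 0.05.

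*Setting B: different assumptions.* Baseline 30, SD 9, within-patient correlation 0.6, linear 12-point fall, last score at week 1, 69 per arm, 4,000 runs.

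- g = 12 × 3/4 = 9. With no effect and 30% vs 14% missing: 0.16 × 9 = 1.44 points, type I error about 0.175.
- Flat scores with 30% vs 14% missing: bias 0, type I error 0.046.
- Now a true difference of −4.5. The plan's f = 0.25 is d = 0.5 for two equal groups, and 0.5 × 9 = 4.5. IBPP falls 16.5 points, so g(IBPP) = 16.5 × 3/4 = 12.375 and g(TAU) = 9.
  - 22% in both arms: bias 0.22 × (12.375 − 9) = +0.74, so −4.5 becomes about −3.8.
  - 30% IBPP / 14% TAU: bias 3.71 − 1.26 = +2.45, giving about −2.0.
  - 14% IBPP / 30% TAU: bias 1.73 − 2.70 = −0.97, giving about −5.5.

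**Twelve months, only if LOCF supplies status.** Let R be the share in remission earlier, q the share of these who truly maintain it, and l the share lost afterwards. LOCF records recovery as R × ((1 − l) × q + l). Assume R = 0.40 and q = 0.75, so true recovery is 30.0%.

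- Loss 22% in both arms: 0.40 × (0.78 × 0.75 + 0.22) = 32.2% in each, with no spurious difference.
- Loss 30% vs 14%: 33.0% vs 31.4%, a spurious 1.6 points (2.6 points if q = 0.60).
- Relapse: a true 25% among remitters (the comparator rate in the trial cited in the Background) with 22% lost is recorded as 0.25 × 0.78 = 19.5%.

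**The case against.** Four points on the other side have weight.

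1. **Unequal loss alone does not produce bias.** A reader might infer that any difference in dropout biases the result. The formula says otherwise: there is no bias if scores have levelled off or the two products cancel. Excess loss in IBPP is conservative. The plan gives one overall rate, so every split by arm used here is an assumption. This stands, and it makes the point conditional.

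2. **LOCF is not assigned to 12 months.** A reader might infer that lost remitters will be scored as recovered, or that LOCF undoes the mixed model. The text prefers mixed models for long-term outcome and qualifies LOCF; it neither states nor excludes LOCF for 3- or 12-month status. The follow-up interview on symptoms and re-hospitalization may also supply status for some patients. The long-term consequence therefore holds only for a patient with no later data, and only if LOCF is used there. It would undo the mixed model only if values were filled before fitting.

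3. **Non-completion is not missing data.** Dropout is defined by sessions attended, and the one-month assessment is planned whether or not the patient is still in hospital. A patient with few sessions can still have a one-month MADRS. The true missing share may be well below 22%, and the figures above are illustrations.

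4. **The completer analysis is a partial check.** Under completely random loss it would tend to expose the artefact simulated here. It does not correct the intention-to-treat result, and it is not protected if loss is related to outcome.

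An analysis plan may refine the scope of LOCF. But naming LOCF is a choice this document makes, not a detail it leaves out.

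**Conclusion.** The point holds in conditional form and should be fixed. LOCF is the only named missing-data method, its scope is undefined, and it bears on the one-month intention-to-treat MADRS contrast. If scores are still falling when patients are lost, the bias has the sign of the difference between arms in share missing times change still to come. Under two sets of assumed trajectories with no true effect and 30% versus 14% missing, it is about 1.4 MADRS points, with type I error of 0.14 to about 0.175. Under equal loss and no effect it is zero; under equal 22% loss with a true −4.5, the estimate shrinks to about −3.8. These sizes rest on assumed falls, timing of loss and missing rates that the documents do not give. The documents do not support saying that the trial's result will be biased, or that LOCF will determine recovery at 12 months. They leave both possible, where a better method is available from the same data.

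**What to change.** In the Data analysis section:

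- Delete LOCF as the method for the primary analysis.
- Analyse one-month MADRS in all randomised patients with a likelihood-based mixed model for repeated measures on the observed baseline, weekly and one-month scores, keeping age as a covariate. Entering baseline as the first measurement keeps patients with no later score in the model. This extends to one month the approach the section already prefers for long-term outcome.
- State that LOCF will not supply response, remission, recovery or relapse status at 3 or 12 months, and use multiple imputation for these rates, including the economic primary outcome.
- Add one sensitivity analysis for data missing not at random, for example delta-adjusted or reference-based.

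The cost is wording and some programming. No new data are needed. Recruitment is closed but follow-up is continuing, so the rule can be fixed before the final analysis.

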## Discussion

Despite the large number of studies on treatment of depression, there is a clear lack of controlled research in inpatient psychotherapy during the acute phase of a major depressive episode. Research on brief therapy is important to take into account current short lengths of stay in psychiatry. The current study has the potential to scientifically inform appropriate inpatient treatment. Psychodynamic psychotherapy has shown some promising signs of efficacy but more controlled studies are strongly needed in order to be empirically validated [65]. This is a very important issue, at least for European countries like Switzerland, France or Germany where psychoanalytic psychotherapy remains the most practiced form of therapy. It may also provide indications of appropriate inpatient treatment to countries where inpatient psychiatric research has become difficult due to economic pressure. As for antidepressant drugs and various types of psychotherapy, psychodynamic psychotherapy is unlikely to be a universal therapy for depression and progress depends on identifying its most appropriate ecological niche [66].

This study is the first to address the issue of the economic evaluation of inpatient psychotherapy. Psychotherapy is costly in time and money; thus evidence of the cost-effectiveness and cost-utility of a short adjunctive psychotherapy as an alternative treatment to longer hospitalization or outpatient aftercare would be an important healthcare finding.

The project has a direct impact on the functioning of the inpatient clinical unit. The implementation of a manualized practice (for psychotherapy and psychiatric treatment-as-usual) will help to improve the organization of the inpatient care and to better structure the clinicians’ training.

